## 16.2 Populations for Analyses

Efficacy analyses of primary, secondary and exploratory outcomes will be conducted using the FAS population and the Safety set will be used in all safety analyses.

### *Full Analysis Set (FAS)*

All participants randomized to receive a study intervention (psilocybin vs. active placebo) will be included in FAS.

### *Per Protocol Set (PP)*

All participants randomized to receive a study intervention (psilocybin vs. active placebo) with no relevant protocol deviations will be included in PP. Relevant protocol deviations will be defined in the Statistical Analysis Plan and finalized before breaking the blind. The Per Protocol set will be used in sensitivity analyses for the primary and secondary objectives.

### *Safety set*

All participants who have received study treatment will comprise the overall safety set.

## 16.3 Statistical Hypothesis

The purpose of this study is to compare psilocybin with placebo in treating depression in the population of interest. The null-hypothesis to be tested is:

H0: Psilocybin is equal to placebo with respect to the treatment of depression  
against

H1: Psilocybin is not equal to placebo with respect to the treatment of depression

## 16.4 Statistical Analyses

Descriptive statistics (proportions, means, standard deviation, quartiles) will be used to summarize all demographic data as well as efficacy and safety endpoints. Distributional features

of all measurements will be evaluated, and data transformation (e.g., logarithm, rank transform) will be performed when applicable.

#### 16.4.1 Efficacy Analyses

The difference between psilocybin and placebo in change from baseline to Day 8 in MADRS total score (primary endpoint) will be analyzed for the Full Analysis Set using Analysis of Covariance including treatment as main effect and baseline as covariate. The same method will be applied for all other single measure endpoints. Treatment differences of multiple measurement endpoints will be analyzed by the mixed model repeated measurements analysis (MMRM) method.

Response and remission rate will be analyzed using logistic regression with the baseline measure as a covariate. The adjusted percentage with 95% CI, Odds Ratio with 95% CI and nominal p-values for the treatment comparison will be presented.

Time to initiation of antidepressant will be defined as the time (in days) from day 43 to the date when any antidepressant has been prescribed. Kaplan-Meier plots of time to initiation of antidepressant will be displayed by treatment groups. Time to initiation of antidepressant will be censored at study discontinuation or completion.

If the assumption of normality does not hold for a particular endpoint on the original scale of measurement, nonparametric methods (e.g. Mann Whitney U test, Fisher's exact) or common transformations (e.g., ln, sqrt) of the original data may be used.

P-values less than 0.05 will be considered statistically significant. As default all tests will be two-sided and two-sided 95% confidence intervals will be computed for the treatment difference. However, any hypothesis that includes a direction of change, eg *increased* [11C]UCB-J binding after dosing, will be tested using one-sided test using a significance level of 0.025.

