## 9.2 Randomization

Randomization will occur for participants who have been determined to be eligible for the study and will occur the morning prior to dosing. Following this, participants will be randomized to one of two intervention groups. Participants are randomized in blocks in a 1:1 ratio in a blinded fashion to the psilocybin group or the active control group. The block size will not be shared. Randomization will be done at the site by strictly following a randomization list in sequential order. If a patient is replaced the new patient will be allocated a randomization number with the same treatment while keeping the double blinded allocation. This will be performed by having back-up blinded treatment allocations for each subject in sealed envelopes. These will only be used and opened following withdrawal. Importantly, the allocated treatment will remain blinded for both the withdrawn and replacement subject as well as for the study team.

The master randomization code will be maintained in a secured location until the time of unblinding. Individual emergency envelopes will be available at the site in case the investigator for safety reasons has to break the blind for a specific patient.

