## 16. STATISTICAL ANALYSIS

### 16.1 Power Analysis and Sample Size Determination

The difference between psilocybin and placebo in change from baseline to Day 8 in MADRS total score (primary endpoint) will be analyzed for the Full Analysis Set using Analysis of Covariance including treatment as main effect and baseline as covariate.

Based on prior controlled studies of psilocybin in cancer- related depression and anxiety, a decrease in depression symptoms from baseline to one-week post-dose of at least 30% is expected in the placebo arm. In an open-label study of psilocybin the change in MADRS total score from baseline to 1 week was -23.3. Several clinical studies in the literature report a standard deviation in change in MADRS total score around 10.

A sample size of 15 in each group will have 80% power to detect a difference in means of 11 (the difference between a psilocybin mean,  $\mu_1$ , of -23 and a placebo mean,  $\mu_2$ , of -12) assuming that the common standard deviation is 10 using a two group t-test with a 5% two-sided significance level.

Considering the short duration between treatment and primary endpoint measurement day 8 the risk of withdrawal is considered low. The total sample size is set to 30 patients completing day 15. In case of withdrawals before day 15 additional patients may be randomized to ensure 30 patients included in the primary and secondary analyses. Estimating a maximum of 20% withdrawals, a maximum of 6 additional subjects can be included.

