#### **16.4.5 Subgroup Analyses**

No subgroup analyses will be conducted.

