### 5.3. Descriptive statistics

Demographic, diagnostic, baseline, line of therapy and safety data will be presented using descriptive statistics. Continuous variables will be described by the number of patients with a recorded value, mean with standard deviation and when appropriate also 95% confidence interval (CI), median, upper and lower quartiles and maximum and minimum values. Categorical variables will be reported as number and percentages with 95% CIs. Differences between subgroups will be compared using chi-square tests, and fisher's test if few cases, for categorical variables and using t-test, and non-parametric statistics, for continuous variables. Distributional features of all measurements will be evaluated, and data transformation (e.g., logarithm, rank transform) will be performed when applicable. Missing data will be described in all summaries.

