## 5.6. Exploratory analysis

The Exploratory analysis will be descriptive between-group differences to support the primary and the secondary analysis as described in section 5.3. In addition, independent predictors will be evaluated using linear (continuous outcome), mixed-linear (repeated outcome), logistic (binary outcome) or Cox (time to event outcome) regression models based on the nature of the data.

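### For single-measure exploratory change endpoints, protocol 16.4.1 prescribes ANCOVA with baseline while SAP 5.6 points to unadjusted tests, and neither text says which governs

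*Protocol*

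**What the plan says.** The statistical analysis plan (SAP) follows the protocol in the same file, so the two can be compared directly.

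- **Protocol 16.2** places exploratory outcomes, with primary and secondary ones, under the efficacy analyses on the Full Analysis Set.
- **Protocol 16.4.1** gives ANCOVA with treatment and baseline for the primary endpoint, then: "The same method will be applied for all other single measure endpoints". Endpoints measured repeatedly go to MMRM, for which no baseline covariate is named. Rank tests or transformations are allowed if normality fails.
- **Protocol 5.3 and SAP 3.3** list the exploratory endpoints. The blood and CSF markers have one post-dose value, at Day 15. Anxiety, life satisfaction and psychological flexibility are taken at Days 8, 15, 42 and 365.
- **SAP 5.6**: "The Exploratory analysis will be descriptive between-group differences to support the primary and the secondary analysis as described in section 5.3". It then adds linear, mixed-linear, logistic or Cox regression for independent predictors, without naming the terms in those models.
- **SAP 5.3** has group comparisons by chi-square or Fisher tests "for categorical variables and using t-test, and non-parametric statistics, for continuous variables". It has no covariate, no repeated-measures term, and no rule for choosing between the t-test and the non-parametric test.

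**The concern.** One set of endpoints has two prescribed analyses. For a marker measured once before and once after dosing, the protocol asks for a baseline-adjusted comparison and the SAP for an unadjusted one. Two things are at stake.

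- **Precision.** A t-test on change fixes the slope on baseline at one. When the pre/post correlation is below one this over-corrects, so chance baseline imbalance between two groups of 15 feeds into the estimate and the confidence interval is wider than it need be.
- **Choice.** With ANCOVA, t-test and rank test all available for many endpoints, the method could be picked after the results are seen.

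The biological questions are part of the rationale in protocol 4.4.3, and the synopsis says the exploratory results will go to academic journals.

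**Working it through.** **1. Which section is meant.** SAP 5.6 cites section 5.3. In the SAP that is Descriptive statistics, which fits the word descriptive in SAP 5.6. SAP 5.5 likewise cites its own section 5.4. The reference therefore leads to the t-test and non-parametric comparison.

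**2. The plan's own figure.** Protocol 16.1: "A sample size of 15 in each group will have 80% power to detect a difference in means of 11", "assuming that the common standard deviation is 10 using a two group t-test with a 5% two-sided significance level". Noncentrality = 11 / (10 × √(2/15)) = 3.01 on 28 df, which gives 82.8% power; 14 per arm gives 80.0%. The stated 80% reproduces as a rounded-down minimum. The SD is that of change: "Several clinical studies in the literature report a standard deviation in change in MADRS total score around 10".

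**3. Efficiency.** Let σ be the SD of a single measurement, equal before and after dosing, and r the pre/post correlation.
- Variance of change = 2σ²(1 − r).
- ANCOVA residual variance = σ²(1 − r²).
- Ratio = (1 + r)/2: 0.65 at r = 0.3, 0.75 at r = 0.5, 0.85 at r = 0.7.

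At r = 0.5, matching the precision of ANCOVA with 15 per arm takes 15/0.75 = 20 per arm on change scores, 5 more.

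**4. Power at 15 per arm** (two-sided 5%; allocation 1:1 from protocol 9.2). The documents give no effect size, SD or correlation for any exploratory endpoint, so d (in units of σ) and r are assumptions.
- Change score: noncentrality d / (√(2(1 − r)) × √(2/15)), 28 df.
- ANCOVA: noncentrality d / (√(1 − r²) × √((2/15)(1 + 1/26))), 27 df. The factor 1 + 1/26 allows for chance imbalance in the estimated covariate.

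| d | r | t-test on change | ANCOVA | loss (points) |
|---|---|---|---|---|
| 0.8 | 0.3 | 43% | 58% | 15 |
| 0.8 | 0.5 | 56% | 67% | 11 |
| 0.8 | 0.7 | 78% | 83% | 5 |
| 1.0 | 0.3 | 61% | 78% | 17 |

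A simulation of 4,000 runs at d = 0.8 gave 44/59%, 55/67% and 78/82%. Where power is already high the loss shrinks: at d = 1.0 and r = 0.7 the same formulas give 93% against 95%.

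**5. The same comparison at the MADRS inputs, for scale only.** Hold the SD of change at 10 and the difference at 11. The ANCOVA residual SD is 10 × √((1 + r)/2) = 8.06, 8.66 and 9.22 at r = 0.3, 0.5 and 0.7. Power is 95.0%, 91.8% and 88.3%, against 82.8% for the t-test: a loss of 12.1, 9.0 and 5.4 points before the small covariate allowance. In 20,000 simulated trials, which include that allowance, the t-test gave about 83% and ANCOVA 94.6%, 90.9% and 87.0%; Mann-Whitney on change gave about 80%.

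**6. Repeated endpoints.** Protocol 16.4.1 gives MMRM, while SAP 5.6 through 5.3 gives separate tests. The models differ, but since the protocol states no baseline covariate for MMRM, the contrast of adjusted with unadjusted in steps 3 to 5 does not carry over.

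**The case against.** The strongest reply is that little depends on this. The synopsis keeps exploratory results out of the Clinical Study Report, protocol 16.4.2 and SAP 5.2 ask for cautious, exploratory interpretation, and the trial is not powered on these endpoints. The main imaging marker, [11C]UCB-J binding, is a secondary endpoint. All of that stands and sets the priority.

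A second reply is that SAP 5.6 is fuller than its first sentence. It calls the group differences descriptive and adds regression models that could carry baseline. This stands in part: the SAP is not confined to t-tests. But the section it cites prescribes tests, and the regressions are for predictors with neither treatment nor baseline named, so they do not restore the protocol's treatment comparison.

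Several stronger readings are tempting but not supported:
- *The SAP discards the baseline.* These endpoints are changes, so baseline is subtracted. Only the covariate adjustment is lost.
- *Any rank test contradicts the protocol.* Protocol 16.4.1 allows Mann-Whitney when normality fails, which is plausible for concentrations. The conflict is with the unconditional t-test and the missing rule for choosing.
- *SAP 5.3 brings in subgroup analyses although protocol 16.4.5 says* "No subgroup analyses will be conducted". SAP 5.3 defines no subgroup, and its comparison bears on this point only if the word means the treatment groups. It is loose wording.
- *Two competing results will be reported.* That follows only if both methods are run.
- *ANCOVA fits every exploratory measure.* MEQ, CEQ, EBI and SPIR are collected only after dosing. Protocol 15 says the first MRI session has no task-based fMRI, although protocol 8.5.2 mentions tasks there.

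**Conclusion.** The point holds as a minor inconsistency. For the single-measure blood and CSF change endpoints, protocol 16.4.1 and SAP 5.6 with 5.3 prescribe different analyses and no text ranks them. For the repeated scales the difference is MMRM against separate tests.

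ANCOVA has the smaller error variance for any r below one, given equal pre- and post-dose variances and a common slope. The size is not fixed by the documents. Roughly 5 to 17 points of power is an illustration at 15 per arm, for r from 0.3 to 0.7 and true differences of 0.8 to 1.0 SD of a single measurement. A reader might take 17 points as a ceiling, but it is not one: at r = 0 and a difference of 0.75 SD of change, the loss reaches 29 points before the covariate allowance. Nor is 5 a floor, as the high-power case in the working shows.

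**What to change.** Amend SAP 5.6 to follow protocol 16.4.1:

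- **One post-dose value and a pre-dose value:** ANCOVA with treatment and the endpoint's own baseline, on a log or rank scale if normality fails.
- **Repeated exploratory scales:** MMRM as in protocol 16.4.1. If a baseline covariate is wanted there, it has to be added explicitly, since the protocol does not state one.
- **SAP 5.3 tests:** keep them for descriptive summaries and for measures with no pre-dose value (for example MEQ, CEQ, EBI, SPIR, and task fMRI if protocol 15 is the correct account of the first MRI session).
- **Reporting:** estimates with 95% confidence intervals, labelled exploratory.

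The cost is SAP wording, settled before unblinding. No new data are needed, and each ANCOVA uses one more degree of freedom than the t-test (27 instead of 28 at 15 per arm).

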## 5. Statistical analysis

### 5.1. Power analysis and Sample Size Determination

The difference between psilocybin and placebo in change from baseline to Day 8 in MADRS total score (primary endpoint) will be analyzed for the Full Analysis Set using Analysis of Covariance including treatment as main effect and baseline as covariate.

Based on prior controlled studies of psilocybin in cancer- related depression and anxiety, a decrease in depression symptoms from baseline to one-week post-dose of at least 30% is expected in the placebo

arm. In an open-label study of psilocybin the change in MADRS total score from baseline to 1 week was -23.3. Several clinical studies in the literature report a standard deviation in change in MADRS total score around 10.

A sample size of 15 in each group will have 80% power to detect a difference in means of 11 (the difference between a psilocybin mean, of -23 and a placebo mean, of -12) assuming that the common standard deviation is 10 using a two group t-test with a 5% two sided significance level.

Considering the short duration between treatment and primary endpoint measurement day 8 the risk of withdrawal is considered low. The total sample size is set to 30 patients completing day 15. In case of withdrawals before day 15 additional patients may be randomized to ensure 30 patients included in the primary and secondary analyses. Estimating a maximum of 20% withdrawals, a maximum of 6 additional subjects can be included.

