## 5.5. Sensitivity analysis

The secondary endpoints evaluating changes in (MADRS, MADR-S, SDS, and CGI) score during different/several time points will be conducted by using MMRM models, fitting treatment, timepoint, and a treatment\*timepoint interaction. The models will be built as of the primary endpoint (see 5.4 Primary analysis). Paired t-test will be performed for between-groups comparisons at all time points, and between all time points over time against baseline. Response will be defined as  $\geq 50\%$  decrease (MADRS and MADR-S) compared to the last measurement before dosing, and remission will be defined as a (MADRS and MADR-S) score  $\leq 10$ . In addition, response will also be defined as  $> 10$  points decrease (MADRS and MADR-S) compared to the last measurement before dosing. Response and remission rate at all time points post dose will be analyzed by using Fisher's exact test and univariable logistic regression with odds ratios (OR) and their 95% confidence intervals (CI) and nominal p-values. An additional secondary endpoint will be time to initiation of antidepressant treatment. Time to initiation of antidepressant will be defined as the time (in days) from day 43 to the date when any antidepressant has been prescribed. Subjects will be censored at study discontinuation or completion. The Kaplan-Meier approach will be assessed with the log-rank test.

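### The response and remission models name no small-sample estimator for 15 patients per arm, and the protocol and SAP disagree on the baseline covariate; a default fit would overstate the odds ratios somewhat and sometimes give none

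*Protocol*

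**What the plan says.** Protocol 16.4.1: "Response and remission rate will be analyzed using logistic regression with the baseline measure as a covariate". The promised output is: "The adjusted percentage with 95% CI, Odds Ratio with 95% CI and nominal p-values for the treatment comparison will be presented".

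SAP 5.5 instead combines Fisher's exact test with "univariable logistic regression with odds ratios (OR) and their 95% confidence intervals (CI) and nominal p-values", so the baseline term is absent.

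Protocol 5.1.2 and SAP 3.2 list response and remission as secondary endpoints at every post-dose time point, on both MADRS and MADRS-S. Protocol 5.5.1 defines response as at least a 50% fall from the last pre-dose score and remission as a score of 10 or less.

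The trial is sized on the continuous primary endpoint (Protocol 16.1): "A sample size of 15 in each group will have 80% power to detect a difference in means of 11". Neither document gives an expected response rate, remission rate or odds ratio.

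**The concern.** With 15 patients per arm, the usual maximum-likelihood logistic fit is biased away from an odds ratio of 1. If an arm has no events or only events, it gives no finite odds ratio, no usable Wald interval and no sensible model-based percentage. Both routes in the plan are exposed to this, and neither sets a rule for it. The Fisher option in Protocol 16.4.1 is triggered by non-normality, not by sparse cells.

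The plan implies about 25 time points for each of response and remission, so roughly 50 correlated models. Even a few percent per model makes it likely that some result cannot be estimated, and the remedy would then be chosen after the data are seen. The two texts also target different quantities: a baseline-adjusted odds ratio and an unadjusted one are not the same number, even in a very large sample.

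**Working it through.** **The plan's own figure.** Inputs from Protocol 16.1: 15 per arm, mean changes -23 and -12, SD 10, two-sided 5% t-test. The noncentral t distribution gives 82.8% power with 15 per arm and 79.99% with 14. The stated 80% is reproduced, rounded down.

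**What has to be assumed.** No mean or SD of baseline MADRS is stated, only a screening floor of 22. The plan pairs a placebo fall of 12 with an improvement of at least 30%, which puts the mean baseline at no more than 12 / 0.30 = 40. Mean baselines of 28 to 40 with SD 5, truncated at 22, were therefore tried.

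**Implied event rates.** For a patient with baseline 30:
- Response needs a change of -15 or lower: Φ((-15 + 23)/10) = Φ(0.8) = 79% on psilocybin, and Φ((-15 + 12)/10) = Φ(-0.3) = 38% on placebo.
- Remission needs -20 or lower: Φ(0.3) = 62% and Φ(-0.8) = 21%.

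Averaged over the baseline distribution with mean 30, this gives response 77% v 37% and remission 59% v 22%. The large-sample odds ratio is about 6.1-6.2 in the adjusted model. In the univariable model it is 5.8 for response and 5.2 for remission.

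**Bias of the default fit.** 20,000 simulated trials per scenario, 15 per arm, changes drawn from N(-23, 10) and N(-12, 10), each fit compared with the large-sample odds ratio of the same model. The geometric mean uses finite fits only; the median uses all fits.

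| Model and outcome | Mean baseline | Geometric mean / true | Median / true |
|---|---|---|---|
| Adjusted, response | 28-40 | 1.25-1.30 | 1.20-1.24 |
| Adjusted, remission | 28-32 | 1.24-1.29 | 1.19-1.24 |
| Adjusted, remission | 34 | 1.17 | 1.29 |
| Adjusted, remission | 36 | 1.00 | 1.30 |
| Adjusted, remission | 40 | 0.65 | 2.19 |
| Univariable, response | 28-40 | 1.12-1.14 | 1.04-1.07 |
| Univariable, remission | 28-30 | 1.11-1.12 | 1.06-1.11 |

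Taking repeat simulations and both summaries together, for baselines of about 28-34, the adjusted ranges are 15-30% for response and 7-38% for remission; the univariable response range is 3-15%. At higher baselines the remission ratios mean little, because so many fits are not finite.

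**Non-finite odds ratios.** The chance of no events in an arm is (1 - p)^15. For placebo remission:
- baseline 30, p = 0.217: 0.783^15 = 2.5%
- baseline 34, p = 0.138: 0.862^15 = 10.8%
- baseline 40, p = 0.054: 0.946^15 = 43%

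The adjusted simulations agree: about 1-2% at baseline 28, 3% at 30, 6% at 32, 11% at 34, 19% at 36, 30% at 38 and 45% at 40. For response the figure is 1-4%. At low baselines the usual cause there is an arm of all responders: at baseline 28, 0.795^15 = 3.2% on psilocybin.

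**Firth fit, same covariate.** Always finite. Geometric mean / true is 1.01-1.04 for response; for remission it is 1.01-1.02 at baseline 28-34, 0.95 at 36 and 0.81 at 40.

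**The case against.** Several objections are sound and limit the point.

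- Neither document names maximum likelihood. It is the ordinary default of the software that the SAP lists, and an estimator is often left to programming. But the SAP text is in the same file and does not settle it.
- A reader might infer that the plan's own assumptions imply inflation of a quarter to a third. They do not. No baseline mean or event rate is stated, the figures cover Day 8 only, and the remission bias is unstable and even reverses in finite fits at high baselines. The inflation is also about half or less in the SAP's univariable model.
- A reader might infer that some results could not be reported at all. With an empty cell, the counts, the percentages with intervals (SAP 5.3) and Fisher's p-value all survive. Only the odds ratio and the model-adjusted percentages fail.
- The bias is small beside the sampling error. At 77% v 37%, the standard error of the log odds ratio is √(1/11.55 + 1/3.45 + 1/5.55 + 1/9.45) = 0.81, against a bias of ln 1.25 = 0.22, about a quarter of one standard error.
- Protocol 4.4.3 speaks of refining effect sizes for phase 3, but does not tie that to these odds ratios.
- Firth has costs. In the univariable model it amounts to adding 0.5 to each cell, so 0/15 becomes 0.5/16 = 3.1% and 3/15 becomes 3.5/16 = 21.9%.

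The contradiction over the covariate and the absence of any rule for an empty cell stand despite all of this.

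**Conclusion.** The point holds as a cheap improvement to secondary analyses. The protocol and SAP must be reconciled on the baseline covariate, and the agreed model needs an estimator that works with 15 per arm. The sizes given rest on three things: a default maximum-likelihood fit, which is inferred; the plan's Day 8 mean changes and SD; and an assumed mean baseline. The risk of a non-finite remission odds ratio depends most on that baseline, from about 1% to 45% across the range that the plan's figures allow. The documents do not support any wider conclusion about the trial's efficacy claim, which rests on a continuous endpoint.

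**What to change.** In Protocol 16.4.1 and SAP 5.5, state one model with treatment and the baseline measure as terms. Fit it by Firth penalised likelihood with profile-likelihood confidence intervals for every response and remission time point on both scales. Keep Fisher's exact p-value and the observed counts and percentages alongside.

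Plain Firth pulls predicted probabilities towards 50%. Take any adjusted percentages from the intercept-corrected version, or report the observed percentages instead.

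Cost: a sentence in each document and a software option. Downside: some shrinkage of large odds ratios, with the median about 2-16% below the true value in most scenarios. It is largest for remission at high baselines, where the median was 0.79 of the true value at mean baseline 40.

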After day 42, all participants will be given follow-up visits at Norra Stockholms Psykiatri for up to one year after dosing, to study dedicated physicians or nurses at a frequency determined by the health care professional. If needed to reach/stay in remission, the participants will be provided antidepressant treatment in accordance with the regional guidelines for antidepressant treatment ([https://psykiatristod.se/regionala-wardprogram/depression](https://psykiatristod.se/regionala-vardprogram/depression)). At least monthly the participants will be asked to provide on-line symptom rating data (via 1177.se). At the 365-day visit, symptoms will be evaluated using MADRS, CGI-I and CGI-S. After completing the study (one year or withdrawal), participants will be subject to standard care, including referral in accordance with regional guidelines.

The study outcome measures will be used to assess depressive symptoms, clinical global functioning, functional disability, anxiety symptoms and health-related quality of life. Safety outcome measures will be collected at all assessment time points from the time of consent through the end of study.

To enhance participant safety, the current study proposes to test psilocybin within a “set and setting” (SaS) protocol similar to the protocol that has been used in all modern studies of psilocybin in both diseased and normal healthy populations. The SaS protocol for this study includes: 1) a preparation with session Facilitators (licensed psychologists) prior to dosing; 2) administration of study medications in an aesthetically neutral room under the supervision of two Facilitators who are present throughout the session (with the exception of short, temporary allowances for facilitator breaks; e.g. bathroom breaks); and 3) three post-dose integration sessions during which participants are encouraged to discuss their intervention experience with the Facilitators. To evaluate the Facilitators' adherence to the study manual, and the role of Facilitators' and participants' in-session behaviors for treatment outcome, all five sessions in the trial with Facilitators present will be recorded. The SaS will be identical for those randomized to psilocybin or niacin active placebo.

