### **9.9 Add on antidepressant treatment**

From day 43, as determined by the patients physician (see 9.7), the patient shall be treated in accordance with regional guidelines: [https://psykiatristod.se/regionala-  
vardprogram/depression](https://psykiatristod.se/regionala-vardprogram/depression)

Information on any treatment that has occurred from day 43 to 365 will be extracted from patient records after day 365. Differences in duration (days) until initiation of antidepressant treatment between treatment groups will be analyzed.

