#### **10.4.3 Dropouts**

If a participant withdraws consent, they will be terminated from the study without further follow up. These participants are defined as dropouts. If they withdraw consent prior to or during Baseline they are considered Screen Failures. If they withdraw consent post dosing then study records/data generated until the date consent is withdrawn will remain available for use by the Sponsor and PI.

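### Time to antidepressant initiation is censored at study discontinuation although the event is taken from patient records to Day 365, so observable starts are discarded and the censoring may be informative

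*Protocol*

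**What the plan says.** Time to initiation of antidepressant treatment is a secondary endpoint (protocol section 5.1.2).

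- **Definition.** Protocol section 16.4.1: "Time to initiation of antidepressant will be defined as the time (in days) from day 43 to the date when any antidepressant has been prescribed".
- **Censoring.** The same section: "Time to initiation of antidepressant will be censored at study discontinuation or completion". It specifies Kaplan-Meier plots by arm.
- **Analysis plan.** The statistical analysis plan text that follows the protocol repeats the rule in its section 5.5 (Sensitivity analysis) and adds a test: "Subjects will be censored at study discontinuation or completion. The Kaplan-Meier approach will be assessed with the log-rank test".
- **Data source.** Protocol section 9.9: "Information on any treatment that has occurred from day 43 to 365 will be extracted from patient records after day 365". It continues: "Differences in duration (days) until initiation of antidepressant treatment between treatment groups will be analyzed".
- **Treatment in follow-up.** The synopsis, under Study Description and Overview: "If needed to reach/stay in remission, the participants will be provided antidepressant treatment in accordance with the regional guidelines for antidepressant treatment".
- **Withdrawal of consent.** Under protocol section 10.4.3, follow-up ends when consent is withdrawn, and "study records/data generated until the date consent is withdrawn will remain available for use by the Sponsor and PI".

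**The concern.** The event is read from a source that does not depend on attending study visits, but the clock stops when study participation stops. Participants can leave without withdrawing consent: staff may withdraw them (section 10.3), or they may become unreachable (section 10.4.4). Their later antidepressant start may be in the records, and the written rule ignores it.

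Kaplan-Meier estimates and the log-rank test need the reason for censoring to be unrelated to the event. Nothing in the documents argues that this holds for discontinuation, and no alternative analysis is named for this endpoint. If some participants leave because their depression needs other care, they are removed from the risk set shortly before the event. The endpoint is meant to show how long the effect of a single dose lasts. At stake are the estimated proportion starting treatment in each arm and, if leaving differs by arm, the comparison itself.

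**Working it through.** **Plan's own figure.** There is none for this endpoint: no event count, hazard ratio or power. The only power statement (section 16.1) concerns the primary MADRS endpoint. It reproduces closely (exact t-test power 0.828 at 15 per group) and has no bearing here.

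**Side by side.** Section 9.9 covers treatment from Day 43 to 365 and does not tie the extraction to continued visits. Section 16.4.1 and analysis plan section 5.5 end observation at discontinuation. For anyone who stops visits in between with consent intact, the two differ by all the record time after that date.

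**Inputs from the documents.** 15 per arm; follow-up window 365 − 43 = 322 days; two-sided 5% level.

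**Assumed inputs (the documents give none).** Exponential start times. True one-year starts are p = 0.35 (psilocybin) and 0.70 (niacin). A fraction f of starters leaves one day before starting and is censored.

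**Formulas.** When a fraction f of starters is censored just before the event:
- Kaplan-Meier estimate of one-year starts ≈ 1 − (1 − p)^(1 − f)
- Observed hazard ratio ≈ true hazard ratio × (1 − f_psilocybin) / (1 − f_niacin)

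True hazard ratio = ln(0.65)/ln(0.30) = 0.431/1.204 = 0.36.

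With f = 0.20 in niacin, 1 − 0.30^0.8 = 0.62. With f = 0.20 in psilocybin, 1 − 0.65^0.8 = 0.29. If only niacin starters leave, the hazard ratio is 0.358/0.8 = 0.45.

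Expected starts with full record follow-up are 15 × (0.70 + 0.35) = 15.75. With 20% leaving first in both arms, 15.75 × 0.8 = 12.6 are counted.

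**Simulation, 10,000 trials per scenario:**

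| Starters leaving first (psilocybin / niacin) | Estimated one-year starts (psilocybin / niacin) | Hazard ratio (approx.) | Log-rank power |
|---|---|---|---|
| 0 / 0 | 35% / 70% | 0.36 | 0.51 |
| 20% / 20% | 29% / 62% | 0.36 | 0.44 |
| 0 / 20% | 35% / 62% | 0.45 | 0.32 |
| 0 / 40% | 35% / 51% | 0.60 | 0.15 |
| 40% / 0 | 23% / 70% | 0.21 | 0.76 |

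**No true difference (50% starts in each arm).** With 20% leaving first in both arms, the estimates are about 43% and 43%, the hazard ratio is 1.0 and the log-rank test rejects 5% of the time. With 40% leaving first in the niacin arm only, the estimates are 50% (psilocybin) and 34% (niacin), the hazard ratio is 1/0.6 = 1.67 and the test rejects 14% of the time.

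**Reading.** Absolute use is understated whenever starters leave first. The hazard ratio moves only when that leaving differs by arm, and the direction depends on which arm loses more.

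**The case against.** The strongest case on the other side has five parts.

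1. **Nobody has to leave to be treated.** Antidepressants are available within the study from Day 43 (synopsis; section 9.9). Phase B is light, mainly online ratings and an end-of-study visit, and post-dose participants are encouraged to stay (section 10.4.2). This stands. A reader might infer that patients typically leave in order to get treated, but no passage says so. The likelier routes are loss to follow-up, withdrawal by staff and outside referral (section 17.1.4).

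2. **Censored is not untreated.** A reader might infer that those who leave are counted as untreated. They are not. They leave the risk set and are assumed to share the later hazard of those who remain.

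3. **Bias between arms is not shown.** It needs leaving that is both linked to treatment start and unequal by arm. Section 17.1.4 says worsening may be likelier under niacin, which makes unequal leaving plausible but does not establish it. With equal leaving the hazard ratio is unchanged.

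4. **The records may be thinner than they look.** After consent withdrawal later data are not available (section 10.4.3). For unreachable participants, no passage says whether later records may be used. Someone who has moved or is treated elsewhere may have no entry, and carrying that person to Day 365 as event-free would create a new error. This stands, and the fix has to allow for it.

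5. **The stakes are modest.** This is one of many secondary endpoints without multiplicity adjustment (section 16.4.2), and even full follow-up gives only about 51% power under the assumed rates.

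None of this defends discarding a start that is on record for a participant who has not withdrawn consent.

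**Conclusion.** The point holds as a mismatch between the censoring rule and the data source. The written rule throws away starts that the planned extraction can observe, and it rests on discontinuation being unrelated to the need for treatment, which the documents do not support. If leaving is related to that need, antidepressant use is understated and events are lost. If such leaving also differs by arm, the comparison can be diluted or exaggerated.

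The size cannot be fixed from the documents. The 20% withdrawal figure in section 16.1 concerns withdrawal before Day 15, not Phase B. The start rates and leaving fractions are assumptions, and placing every departure one day before the start is the most informative case. Within those assumptions the hazard ratio of 0.36 ranges from about 0.21 to 0.60, and it does not move when leaving is equal. The documents do not support the stronger conclusion that the arm comparison is biased, or that it is biased towards no difference. The change is worth making because it is cheap. It concerns a secondary endpoint and leaves the primary conclusion untouched.

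**What to change.** In protocol section 16.4.1 and analysis plan section 5.5, replace the censoring sentence with a rule to this effect:

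- Count any antidepressant start found in the patient records up to Day 365, whether or not study visits continue.
- Censor at the earliest of Day 365, death, withdrawal of consent to record use, or the last date on which the records show the participant is still covered.
- Report the analysis with censoring at study discontinuation as a sensitivity analysis.

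Section 9.9 should say that the extraction includes participants who stopped visits without withdrawing consent, and how continued record coverage is judged, so that nobody without coverage is carried forward as event-free.

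**Cost.** A few sentences. Record extraction is already planned, although section 9.9 does not say explicitly that it includes discontinued participants. The drawback is that treatment prescribed outside the record system is missed, more so for participants who no longer attend visits.
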